#### Suspension criteria

2.2.5

(1)In the treatment of this study, the patient was unexpectedly pregnant or had serious adverse reactions, and it was difficult to continue to receive treatment.(2)During the implementation of this study, there was an obvious exacerbation or complications.(Fig. 2)

**Figure 2 F2:**
[figure not shown]
SPIRIT figure for the schedule of enrollment, interventions, and assessments. CTPI = computed tomography perfusion imaging, NIHSS = National Institutes of Health Stroke Scale, SPIRIT = Standard Protocol Items: Recommendations for Interventional Trials.

### Interventions

2.3

#### Different interventions given in two groups

2.3.1

The control group will be given basic Western medicine treatment. The course of treatment was 2 weeks, and the effect was observed after 2 weeks. Followed up to 3 months after onset. We will refer to the “Chinese Guidelines for the Diagnosis and Treatment of Acute Ischemic Stroke 2018 Edition” for the treatment of cerebral infarction formulated by the Chinese Medical Association Neurology Branch. Specific plans are: aspirin 100 mg, clopidogrel hydrogen sulfate 75 mg, orally once a day before bedtime; and routine nutritional nerves, lowering fat density, and improving microcirculation treatment for patients with acute stage of cerebral infarction; related to other diseases Specialist treatment, but it should be noted whether the medication affects the effect of the test drug and recorded in detail. The intervention group will be given TCM cooperative therapy. In addition, the two groups will be given basic Western medicine treatment at the same time. If there are hypertension, coronary heart disease, diabetes, infection, electrolyte disturbance and other symptoms, we will give routine treatment and symptomatic treatment.

#### CT volume cerebral perfusion imaging

2.3.2

All patients will undergo conventional CT plain scan and spiral CT brain perfusion imaging examination. We will use Siemens dual-source CT *(Device model: Somatom Definition Flash, device number: 73396)* for operation. After the conventional craniocerebral CT scan, the DynMulti4D scan mode was used for VPCT scan. A double-barreled high-pressure syringe will be used to inject an iohexol 50 ml through an anterior cubital vein 18–20G at a flow rate of 5 ml/s. 40 ml of normal saline will be injected at the same flow rate; continuous dynamic scanning will be started 21 times 5 s after the contrast injection, and the scanning time is 35.54 s. Scanning parameters: tube voltage 80 kV, tube current 120 mAs, scanning range 100 mm, tube rotation time 0.28 s/rev, collimator width 128 × 0.6 mm. Automatic reconstruction of 5 mm and 1 mm axial image, 1 mm The axial image is automatically transferred to the workstation. Image evaluation: The scanned images need to be processed by software in order to obtain information such as cerebral flow and cerebral blood volume on the lesion side, contralateral side, and other parts.

#### CT Image post-processing

2.3.3

The 5 mm perfusion image will be post-processed with the Neuro PCT software package on the scanning table. The software automatically generates three-dimensional VPCT parameter maps: cerebral blood flow (CBF), cerebral blood volume (CBV), mean transit time (MTT), and time to drain (TTD). The 1 mm layer CTA data will be post-processed on the workstation using Inspace software to obtain 21 periods of dynamic CTA images (4D-CTA). Post-processing methods include VRT, MIP, and MPR.

### Outcome measures

2.4

#### Primary outcome measures

2.4.1

The primary outcome measure will be evaluated using CT imaging parameters. Brain CTPI parameters collection method: Siemens dual-source CT *(Device model: Somatom Definition Flash, device number: 73396),* CTPI imaging examination of patients with unknown onset time. The opposing areas of the cerebral hemispheres on both sides are measured to quickly determine if there is a reversible ischemic zone. Using a high-pressure syringe, a nonionic contrast agent is injected into the patient's anterior cubital vein. Then, a single layer of continuous dynamic scanning is performed on the selected layer. The resulting image is processed by Siemens CTPI software package for subsequent processing. We will use the midline of the brain as the mirror to select the area of interest, and measure the lesion area and the corresponding area on the opposite side symmetrically. We will use this method to obtain cerebral blood flow (CBF), cerebral blood volume (CBV), and mean transit time (MTT) at different levels on both sides of the brain.

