**Methods/design::**

This study plan randomly divided eligible acute cerebral infarction patients into two groups. Patients in the control group will be treated with conventional Western medicine; patients in the intervention group will be treated with traditional Chinese medicine cooperative therapy on the basis of conventional Western medicine. The curative effects will be selected before treatment, 2 weeks after treatment, and 3 months follow-up. The changes in CT imaging evaluation, NIHSS score, and BI index of the two groups of patients will be observed.

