### CT Imaging evaluation method

2.5

The CTPI images collected in all cases will be evaluated blindly by 2 physicians who have more than one diagnosis. After jointly determining the perfusion abnormal area and reaching an agreement, the region of interest (ROI) is manually drawn. The ROI selects the center of the lesion, and simultaneously draws the contralateral mirror area on the centerline symmetry axis. When the symmetry area is an abnormal perfusion, the normal area of the contralateral same-layer perfusion parameter map is selected as the contralateral mirror area. CBV, TTD, and MTT values. Infarct focus was based on review of MRI DWI high signal area. The degree of stenosis of the responsible vessels was also evaluated.

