### Statistical analysis

2.7

SPSS for windows 24.0 statistical analysis software will be used for calculation, and normality test and homogeneity test of variance will be performed on each group of data. For measurement data in which the data conforms to the normal distribution, we will use the mean ± standard deviation. For nonnormally distributed measurement data, the median ± quartile interval is used. General data comparison between the two groups using independent sample T test. Comparisons before and after treatment will be performed using t test for paired data. One-way analysis of variance will be used for comparison between groups. X^2^ test will be used for count data, and nonparametric rank sum test will be used for rank data. All statistical tests are two-sided. *P* < .05 indicates a significant difference.

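### The primary outcome is an unranked set of three CT perfusion parameters with no chosen summary or time point, and every test is judged at two-sided P < .05

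*Protocol article*

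**What the plan says.** Section 2.4.1 opens with "The primary outcome measure will be evaluated using CT imaging parameters". It then lists what is collected, for both hemispheres: "We will use this method to obtain cerebral blood flow (CBF), cerebral blood volume (CBV), and mean transit time (MTT) at different levels". No parameter is put ahead of the others, no per-patient summary is defined, and no visit is named.

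The abstract (Methods/design) gives the assessment times: "The curative effects will be selected before treatment, 2 weeks after treatment, and 3 months follow-up". It includes CT evaluation among the changes to be observed in the two groups. Section 2.3.1 describes a 2-week treatment course with the effect observed at its end, and then follow-up to 3 months after onset.

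Section 2.7 compares groups by one-way analysis of variance and sets a single threshold: "All statistical tests are two-sided. *P* < .05 indicates a significant difference".

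Two other statements bear on what the primary set is:
- Section 2.5, the reading procedure, names "CBV, TTD, and MTT values". TTD is not in the section 2.4.1 list, and CBF is missing from section 2.5. Section 2.3.3 has the software produce all four.
- Section 2.4.1 itself says "a single layer of continuous dynamic scanning is performed on the selected layer", two sentences before the sentence that refers to values at different levels.

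**The concern.** A primary outcome has to tell the reader, before any data exist, which result would support the main claim. Here three parameters share that place without rank, so the article does not say whether a difference in MTT alone, with none in CBF or CBV, would count as a positive trial. With the same .05 threshold for each comparison, the plan as written does not stop the primary claim from resting on whichever parameter or visit happens to fall below it. The 5% error rate would then hold for each test separately but not for the trial's main conclusion.

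The disagreement between sections 2.4.1 and 2.5 makes this worse, because even the membership of the set is open.

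**Working it through.** The article states no sample size, power or overall error rate, so there is no figure of its own to reproduce beyond the per-test .05.

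**Inputs from the document**
- Per-test level: .05, two-sided (section 2.7), so the critical value is c = 1.96.
- Parameters in the primary outcome: 3 (section 2.4.1).
- Post-treatment times: 2 weeks and 3 months (abstract). The text does not state outright that perfusion CT is repeated at both, and the schedule figure (Figure 2) was not available for this check. One visit and two visits are therefore both computed.

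**Assumptions, not in the document**
- One significant between-group comparison is enough to claim success.
- Test statistics are jointly normal with a common correlation ρ between 0 and 0.8.

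**Formulas for k tests**
- Independent tests: 1 − 0.95^k.
- Common correlation ρ: 1 − ∫ φ(x) [Φ((c − √ρ·x)/√(1−ρ)) − Φ((−c − √ρ·x)/√(1−ρ))]^k dx, by numerical integration.

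For independent tests:
- k = 3: 1 − 0.95³ = 1 − 0.8574 = 14.3%
- k = 6: 1 − 0.95⁶ = 1 − 0.7351 = 26.5%

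| Tests counted | ρ = 0 | 0.5 | 0.7 | 0.8 |
|---|---|---|---|---|
| 3 parameters, one visit (k = 3) | 14.3% | 12.5% | 10.9% | 9.8% |
| 3 parameters, two visits (k = 6) | 26.5% | 20.7% | 16.4% | 13.9% |

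A simulation of the six-test case with separate correlations between parameters and between visits gave 16.0% (parameters 0.8, visits 0.7) to 23.5% (parameters 0.3, visits 0.5), inside the second row's range.

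**Sensitivity to a larger set**

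| Tests counted | ρ = 0 | 0.5 | 0.7 | 0.8 |
|---|---|---|---|---|
| TTD added, one visit (k = 4) | 18.5% | 15.6% | 13.0% | 11.4% |
| TTD added, two visits (k = 8) | 33.7% | 25.0% | 19.1% | 15.7% |
| 3 parameters, two visits, two levels tested separately (k = 12) | 46.0% | 31.9% | 23.2% | 18.6% |

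The second table shows only the direction of travel. Section 2.4.1 does not list TTD, and the number of levels is not stated anywhere.

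**After the fix**
- One named variable at one time has an error rate of 5%.
- For three co-primary parameters, Holm compares the ordered p-values with .05/3 = .0167, .05/2 = .025 and .05, and keeps the total at or below .05 whatever the correlation. Its first step is the Bonferroni threshold; for three independent tests, 1 − (1 − .0167)³ = 4.9%.

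**The case against.** The strongest reply is that this is a condensed article. A multiplicity procedure and the rule for summarising region-of-interest readings are commonly left to the full protocol or the SAP, neither of which is shown, and .05 is a conventional threshold rather than a rule for declaring success. That stands in part: silence on multiplicity is not the finding, and the error rates above are conditional on an any-one-wins reading. But the choice of primary variable and time is a protocol matter. The article has a section for the primary outcome and fills it with an unranked set that its own reading procedure contradicts.

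Two further points also have weight:
- Section 2.3.1 can be read as making 2 weeks the efficacy time. If so, the one-visit row applies.
- The parameters come from the same scans and regions of interest, so independence is unlikely and the upper ends of the ranges are bounds rather than expectations.

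Two stronger readings are tempting, and the documents do not support them:
- A reader might infer that the error rate reaches about a third. That needs eight independent tests, with TTD as a fourth primary parameter and CT compared at both visits. TTD is outside the section 2.4.1 list.
- A reader might infer that several levels from one patient will enter the tests as separate observations, breaking independence. Nothing in section 2.7 says so. Section 2.5 describes an agreed region of interest at the lesion centre with a mirror area, which is compatible with one value per patient.

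**Conclusion.** The point holds in a conditional form. The article makes CBF, CBV and MTT jointly primary without choosing a parameter, a per-patient summary or a time, and judges every test at two-sided .05. If any one significant parameter counts as success, the false positive rate for the primary claim is about 10% to 14% at one visit, roughly two to three times nominal. It is about 14% to 26% if CT is compared at both post-treatment visits. These ranges rest on the assumed success rule and on assumed correlations from 0.8 to 0, and they would rise if TTD or separate levels were also tested. In every case computed the rate exceeds 5%, so the need for a change does not depend on the exact correlation or on the number of visits.

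Separately, and without any assumption, sections 2.4.1 and 2.5 give different parameter lists, and section 2.4.1 speaks of both one layer and several levels.

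**What to change.** First reconcile sections 2.4.1 and 2.5 on which parameters are read, and state whether one layer or several levels are measured. Then choose one of two routes:

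1. **Single primary.** Name one variable with one value per patient, for example the lesion-to-mirror ratio of one chosen parameter, with a stated rule for combining levels if more than one is read. Name one time, for example 2 weeks, the end of the treatment course in section 2.3.1. Make the other parameters and times secondary. The choice of parameter is the sponsor's, but it must appear in the reading procedure as well as in the outcome section.
2. **Co-primary.** Keep the three parameters, each with one value per patient, at that one time, and test them by Holm's procedure at a total of .05.

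Sections 2.9 and 3.1 say recruitment has not started, so the change costs only wording in the protocol and the registry entry. The price is fewer routes to a positive result. Under the second route the smallest p-value must also fall below .0167 before any parameter can be declared significant, which costs some power for each parameter. Once CT results have been seen, the same choice would no longer be credible.

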#### Secondary outcome measures

2.4.2

The National Institutes of Health Stroke Scale (NIHSS) will be used to assess the neurological function of patients with ACI, and the Barthel Index (BI) score was used to assess the ability of daily living.

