## Introduction

1

Acute cerebral infarction (ACI) is a clinically common cerebrovascular disease. ACI is characterized by sudden onset, dangerous illness, high risk of death, and disability.^[1]^ In recent years, the incidence of cerebrovascular disease has gradually increased. According to the WHO Global Disease Data Report, cerebral infarction is the third leading cause of death among residents worldwide, and it is also a major cause of disability.^[2,3]^ In recent years, the increase in the number of patients with acute cerebral infarction may be related to life, work, psychological stress, and incontinent diet. In addition, atherosclerosis and cardiogenic embolism are the two most common causes of cerebral infarction.^[4]^ The former can cause narrowing of the arterial lumen, leading to brain tissue necrosis. Another common cause of cerebral infarction is cardiogenic embolism. Most embolic emboli will stagnate on the head and cause ACI.

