#### Inclusion criteria

2.2.2

(1)Those who meet the ACI diagnostic criteria for Western medicine;(2)Those who meet the diagnostic criteria for stroke in Chinese medicine;(3)The time from onset to admission for treatment is within 72 hours;(4)The National Institutes of Health Stroke Scale (NIHSS) score is ≥6 points and ≤22 points;(5)Patients with first onset of ACI or patients with recurrent stroke have fully recovered before the onset of this disease;(6)Those who voluntarily accept the clinical observation of this project and sign the informed consent;

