#### Safety observation measures

2.4.3

(1)General physical examination items, such as body temperature, heart rate, respiration, blood pressure, and blood sugar.(2)Possible adverse events and the incidence of adverse events.

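### No efficacy outcome captures death and death is not a named safety outcome, so the later CT perfusion, NIHSS and Barthel comparisons are in effect limited to survivors and can favour the arm with more deaths

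*Protocol article*

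**What the plan says.** **Disease and population.** The Introduction states that "ACI is characterized by sudden onset, dangerous illness, high risk of death, and disability". Inclusion criterion 4 (section 2.2.2) reads: "The National Institutes of Health Stroke Scale (NIHSS) score is ≥6 points and ≤22 points".

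**Follow-up.** Section 2.3.1 says "Followed up to 3 months after onset". The abstract gives the assessment times: "The curative effects will be selected before treatment, 2 weeks after treatment, and 3 months follow-up".

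**Outcomes.** Section 2.4.1: "The primary outcome measure will be evaluated using CT imaging parameters", namely CBF, CBV and MTT. Section 2.4.2: the NIHSS score "will be used to assess the neurological function of patients with ACI, and the Barthel Index (BI) score was used to assess the ability of" everyday activity. Section 2.4.3 lists general physical measurements and "Possible adverse events and the incidence of adverse events". Death is not named in any of the three lists.

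**Analysis.** Section 2.7 plans paired t tests before and after treatment, one-way analysis of variance between groups, a chi-square test for counts and a rank sum test for ranked data. It gives no value to a patient who has died.

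**Removal of cases.** Section 2.2.4 includes serious adverse events among the reasons for rejecting or shedding a case. Section 2.2.5 suspends patients for marked worsening or complications.

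**The concern.** The article stresses mortality and sets out to evaluate both efficacy and safety, but nothing it plans to measure isolates death. A CT perfusion parameter, an NIHSS score and a Barthel score can be obtained only from a living patient.

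Those who die by 3 months are likely to include many with the worst prognosis. If they contribute no later score, the survivors of the arm with more deaths are a better-selected group. Their average function then looks better without any treatment effect. The error runs in the dangerous direction: a treatment that increased deaths could appear to improve function in those left.

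The safety section would not reliably correct this impression. A death counts there as one adverse event among all others, so a difference in mortality can be hidden by events of far less weight.

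**Working it through.** **No figure to reproduce.** The article gives no death rate, SD, effect size or sample size for these outcomes. The calculation below only illustrates direction and size.

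**Inputs from the documents.** All efficacy outcomes need a living patient (2.4.1, 2.4.2). The t tests and analysis of variance use observed values (2.7). A serious adverse event is a ground for removing the case (2.2.4).

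**Inputs that are assumptions.** Death rates d of 5% in one arm and 10% or 15% in the other; a correlation ρ of 0.5 or 1 between the severity that leads to death and the 3-month score; a Barthel SD of 30 points.

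**Model.** The 3-month score, had everyone lived, has the same normal distribution in both arms, so there is no true effect. A patient dies if severity lies in the worst fraction d. The survivor mean then looks better than the full-population mean by

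ρ × φ(z) / (1 − d) SD,

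where φ is the standard normal density and z is the normal quantile that cuts off d.

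**Step 1, ρ = 1.**
- d = 5%: 0.109 SD
- d = 10%: 0.195 SD
- d = 15%: 0.274 SD

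**Step 2, difference between arms, in favour of the arm with more deaths.**

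| Deaths | ρ = 0 | ρ = 0.5 | ρ = 1 |
|---|---|---|---|
| 5% v 5% | 0 | 0 | 0 |
| 5% v 10% | 0 | 0.043 SD | 0.086 SD |
| 5% v 15% | 0 | 0.083 SD | 0.166 SD |

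A simulation with 2,000,000 patients per arm agrees with these values to within 0.003 SD.

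**Step 3, Barthel points at an assumed SD of 30.**
- 5% v 10%: 0.043 × 30 = 1.3 points (ρ = 0.5) to 0.086 × 30 = 2.6 points (ρ = 1)
- 5% v 15%: 0.083 × 30 = 2.5 points (ρ = 0.5) to 0.166 × 30 = 5.0 points (ρ = 1)

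For the Barthel Index the distortion is a higher survivor mean; for the NIHSS, where lower is better, it is a lower one. The column ρ = 1 is an upper bound, since it makes the dead exactly the patients who would have scored worst. For CT perfusion the same formula applies, but the documents give no link between prognosis and later perfusion, so no size can be put on it.

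**The case against.** **Death is not wholly uncounted.** A reader might infer that no outcome registers death at all and that patients who die vanish from every comparison. The documents do not support that. A death falls within the adverse-event incidence of section 2.4.3, and section 2.7 provides a chi-square test for counts. What stands is narrower: death is not separated there, and no efficacy outcome includes it.

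**Survivor-only analysis is inferred.** The article states no analysis set, and the treatment of unobserved scores may be set in a full protocol or analysis plan that is not shown. That is fair as to the handling of missing values. It does not dispose of the point, because which outcomes a trial measures is fixed in section 2.4, and mortality cannot be compared reliably later unless vital status is collected on everyone, including patients shed or suspended. Section 2.2.4 also points towards removal, since a death is a serious adverse event.

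**Mortality may be modest here.** The statement on risk of death concerns the disease in general. Section 2.2.3 excludes large infarcts with unstable vital signs and severe organ disease, which plausibly removes many of the likeliest deaths. This stands: the documents give no death rate for the enrolled population, and the rates above are assumed.

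**The bias is conditional.** It needs unequal deaths that are related to the outcome. This stands too, and is why the result is given as a range that includes zero.

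**Conclusion.** The point holds in this form: no efficacy outcome captures death, death is not named as a separate safety outcome, and the listed outcomes, tests and shedding rule together leave later-visit efficacy comparisons that rest in effect on survivors. These can favour the arm in which more patients die.

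The size is small to moderate, about 0.04 to 0.17 SD, under death rates, a correlation and an SD that are all assumed. It would be wrong to conclude that the trial will be biased by this amount, or that deaths will go unrecorded. The change is still worth making, because the possible error hides harm, the article itself stresses mortality, and its Trial status section says recruitment has not started.

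**What to change.** 1. **Section 2.4.3:** name all-cause death up to 3 months after onset as an outcome. Collect vital status, with date of death, for every randomised patient, including those shed under 2.2.4 or suspended under 2.2.5. Compare it by arm among all randomised patients.
2. **Section 2.4.2:** for NIHSS and Barthel at visits after a death, rank death as worse than every score in a survivor, and compare the arms with the rank sum test already listed in 2.7.
3. **Section 2.4.1:** label later CT perfusion results as results in survivors and show them beside deaths by arm.
4. **Section 2.2.4:** state that rejection or shedding does not remove a patient who died from the comparisons in items 1 and 2. Without this, the present rule would contradict them.

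**Cost.** Protocol wording and a vital-status entry with date on the case report form. The NIHSS and Barthel results would no longer read as a mean change in survivors. Ranking is one of several acceptable ways to include death; it is suggested because the test is already in the plan. The primary CT perfusion comparison stays survivor-only even after the change, so it must be read together with mortality.
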